#### Concealment of Allocation and Blinding

While participants in the experimental group should notice the novel prevention pop-up messages, for all they know before debriefing, there is no “assignment” per se. This is because the study is presented as an opinion survey about the realism of the bar replica and the gambling session in it. No instruction suggests any type of comparison between conditions. Therefore, participants would not be aware that there are 2 different groups, nor that this study tests the effects of prevention pop-up messages.

Note that masking becomes “open label” after debriefing. Indeed, after being informed of the true goals of this study, participants are easily able to determine in which group they were allocated based on what occurred during their gambling session. Regardless, gambling behaviors are recorded before debriefing and would not be affected by unmasking. There is no functional way to mask group assignment to the research team. However, the randomization procedure ensures that allocation is purely random.

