### Experimental Group: Regular Gambling Session With Prevention Pop-Up Messages

This condition is the same as the active control group with the addition of prevention pop-up messages delivered during the gambling session on a fixed presentation schedule.

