### Postexperimentation Phase

The participant is brought in a separate office after the end of the gambling session for a series of questionnaires (outcomes listed in “Secondary Outcome” and “Other Outcomes” sections) which are, in order:

Evaluation of participants’ perception of the realism of the bar replica and of the gambling session.Evaluation of participants’ ability to recall prevention pop-up messages. This includes multiple tasks of free recall (eg, describing the pop-up messages from memory) and cued recall (eg, selecting from a list the pop-up messages that were seen during the gambling session).Evaluation of participants’ cognitive and emotional response to prevention pop-up messages.Evaluation of protocol credibility (ie, if the participant really believed they were gambling their own money and were really risking their own money).

These questionnaires are comprised of Likert scales, multiple-choice questions, and open-ended questions. Contrary to more standard qualitative designs, open-ended question responses are not recorded in an audio format, nor are they transcribed verbatim [82]. Instead, the interviewer takes notes, which the participant can see on a computer screen. Participants are then asked to confirm that the interviewer’s notes accurately reflect their opinion. It has been suggested that note-taking is superior to audio recording for obtaining qualitative data [83].

Debriefing about the true goals of the study and final validation of consent to participate in the study are done between the evaluation of participants’ perception of the realism and the evaluation of participants’ ability to recall prevention pop-up messages.

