	16	Perceived behavioral effectiveness of prevention pop-up messages	Participant’s perceived effectiveness of prevention pop-up messages on modifying their gambling behavior during the gambling session. Evaluated with two 7-point Likert scales about the perceived effects of the prevention pop-up messages on money betted and time spent during the gambling session (1=“lowered gambling behavior a lot” to 7=“heightened gambling behavior a lot”).	Assessed at the end of the gambling session.
Emotions				
	17	General level of fun while gambling on EGMs	Participant’s general enjoyment of gambling on EGMs over the gambling session’s total duration. Evaluated with a 7-point Likert scale (1=“I hated it” to 7=“I loved it”).	Assessed at the end of the gambling session.
	18	Change in general level of fun while gambling on EGMs	Change between self-reported measures (past 12 months) and observed data in the laboratory.	Past 12 months; end of the gambling session.
	19	Psychological reactance to prevention pop-up messages (between group)	Evaluated based on Dillard and Shen [84] method: (1) Induction check (4 items, 7-point Likert scale, 1=“Strongly disagree, 7=“Strongly agree”); (2) Anger (4 items, 7-point Likert scale, 1=“Strongly disagree, 7=“Strongly agree”); (3) Cognitive response (count of negative thoughts in relation to the pop-up messages); and (4) Attitude (7 word pairs, 7-point semantic differential scale).	Assessed at the end of the gambling session.

a EGM: electronic gambling machine.

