	31	What could be done to heighten the realism of the session in the laboratory	Things or aspects of the study that could be changed in order for the gambling session in the laboratory to be more like a real gambling session on EGMs in a bar or restaurant. The participant lists all that come to their mind.	Assessed at the end of the gambling session
	32	Effect of using one's own money on realism	Effect of gambling one’s own money in this study on the level of realism. Evaluated with a 7-point Likert scale (1=“It lessened the realism a lot” to 7="It heightened the realism a lot").	Assessed at the end of the gambling session
	33	Effect of using one's own money on realism (open-ended)	Effect of gambling one’s own money in this study on the level of realism. Participants freely explain their perception of the said effect.	Assessed at the end of the gambling session
	34	Perceived correspondence between habitual gambling behavior and gambling behavior during the session in the laboratory	Participant’s perception of how much their gambling behavior during their gambling session in the laboratory was representative (ie, how much it was the same) of their gambling behavior on EGMs in the past 12 months. Evaluated with a 7-point Likert scale (1=“Almost 100% different” to 7=“Almost 100% the same”).	Assessed at the end of the gambling session
	35	Perceived correspondence between habitual gambling behavior and gambling behavior during the session in the laboratory (open-ended)	Participants’ perception of how much their gambling behavior during their gambling session in the laboratory was representative (ie, how much it was the same) of their gambling behavior on EGMs in the past 12 months. Participants freely explain their perception.	Assessed at the end of the gambling session
Feasibility: Duplicity check
	36	Protocol credibility	Participant’s level of certitude when they were betting their own money and that they could lose money for real during the study. Evaluated with a 7-point Likert scale (1=“Almost 100% certain they were going to get their money back at the end of the study” to 7=“Almost 100% certain winnings and losses were real”).	Assessed at the end of the gambling session
	37	Protocol credibility (open-ended)	Participants comment freely on their level of certitude that they were betting their own money and that they could lose money for real during the study.	Assessed at the end of the gambling session

a N/A: not available.

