### Statistical Methods

Sociodemographic variables, past 12 months of gambling-related variables, and PGSI category will be presented in a table with appropriate central tendency estimates. This table will be divided by assignation group.

A total of 3 statistical models will be used to analyze the outcomes presented in Tables3  4. All these models will control for the time-varying covariate “gains-losses differential” (ie, remaining balance on the EGM at measured time point minus money inserted in the EGM from the start of the study). All models will also test the moderation effect of the following variables: gender (men or women), age (continuous), education (5 categories), and PGSI category (nonproblem, low risk, and moderate risk). Holm-Bonferroni correction [85] will be used to counteract family-wise error rate due to multiple comparisons in each model for each statistically significant categorical variable (ie, time for repeated measures ANCOVAs; moderators with ≥3 categories).

The first model uses ANCOVAs to examine the differences between the two groups at the end of the gambling session on outcome variables 1, 3, 4, 6‐9, 14, 16, 17, and 19, separately.

The second model uses repeated measures ANCOVAs to examine the differences between the two groups at specific time points during the experiment corresponding to the presentation of the prevention pop-up messages in the experimental group. This model is computed on outcome variables 1 and 10‐13, separately.

The third model uses repeated measures ANCOVAs to examine the differences between self-reported measures (past 12 months) and the observed behaviors during the experiment. This model is computed on outcome variables 2, 5, 15, and 18, separately.

Secondary and other outcomes will be documented but will not be statistically compared. Descriptive estimates will be provided for each quantitative variable. Open-ended questions will be analyzed in a manner inspired by the thematic analysis method (see Textbox 3) [86].

Textbox 3.The 5 steps in analysis of open-ended questions.Interviewer’s notes are regrouped in a Microsoft Word document.Raw data is carefully read, both by main author and another member of the research team, to extract categories of similar content.Categories are refined by both coders.Raw data is independently categorized in appropriate categories by both coders.Intercoder agreement is calculated on all categorizations to ensure reliability.

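### Primary outcome 16, and outcome 19 unless its control stimulus is defined, cannot be compared between arms as message effects, because controls see no prevention message

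*Protocol article*

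**What the plan says.** Table 3 of the protocol article (Outcome Assessments) lists 19 primary outcomes. Outcome 16 is defined as "Participant’s perceived effectiveness of prevention pop-up messages on modifying their gambling behavior during the gambling session", rated on two 7-point scales, one for money and one for time. Outcome 19 is titled "Psychological reactance to prevention pop-up messages (between group" and has four components: induction check, anger, "Cognitive response (count of negative thoughts in relation to the pop-up messages" and attitude.

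Statistical Methods states: "The first model uses ANCOVAs to examine the differences between the two groups at the end of the gambling session on outcome variables". The list that follows includes 16 and 19. The same section has every model test moderation by gender, age, education and PGSI category.

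On exposure, the description of the experimental group reads: "This condition is the same as the active control group with the addition of prevention pop-up messages delivered during the gambling session".

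On timing, Postexperimentation Phase gives four questionnaires in order: realism, recall of messages, cognitive and emotional response to messages, and protocol credibility. It adds: "Debriefing about the true goals of the study and final validation of consent to participate in the study are done between the evaluation" of realism and that of recall. Concealment of Allocation and Blinding accepts that participants can work out their arm once debriefed, and answers that "gambling behaviors are recorded before debriefing and would not be affected by unmasking".

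**The concern.** Outcome 16 asks about the effect of something that did not happen to half of the participants. A control value is either missing or a rating of an event that never occurred, yet the plan tests the difference between arms. Outcome 19 raises the same question, because the article does not say what controls are asked to react to.

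A significant result on either would invite the reading that the messages changed behaviour or provoked reactance. The Discussion gives these outcomes weight: it proposes reactance as an explanation if the behavioural results are negative.

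The probable timing adds to this. The section on ecological validity warns that demand characteristics can inflate the apparent effectiveness of such measures, and preventing them is one reason given for the deception. Asking people how well the messages worked, just after telling them that the messages are the subject of the study, reopens that route for these outcomes.

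**Working it through.** The article's numerical figures (sample size and power) do not bear on this point. The check traces exposure, question, timing and model, and ends with a count.

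1. **Exposure.** The arms differ only in the prevention pop-ups, so a control has no in-session prevention message.

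2. **What a control could be rating.** The article offers two candidates.
   - The machine's built-in time limit reminder (Mandatory Time Limit Reminder). It is present in both arms and is not one of the study's prevention messages.
   - The message texts on the cued-recall list (Table 5, outcome 41). Controls may read these, but only after the session and after debriefing.

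3. **Outcome 16.** It asks about an effect on behaviour during the session. Neither candidate supplies that, so the control value is undefined and the ANCOVA contrast cannot be a message effect.

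4. **Outcome 19.** The title and the negative-thoughts component name the messages. The other three components are listed without an object of their own. If controls rate the recall-list texts, an object exists, but the contrast is then between exposure during play and reading afterwards. That is not reactance to in-session messages.

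5. **Timing.** The stated order is realism, debriefing, recall, cognitive and emotional response, credibility. Outcomes 16 and 19 match the fourth of these steps by subject, which puts them after debriefing. This is an inference: Table 3 says only that they are assessed when the session ends, and the sentence introducing the questionnaires refers to the secondary and other outcomes. In alternative scenarios 2 and 3 (Gambling Session in the Laboratory) debriefing comes even earlier.

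6. **Masking.** After debriefing participants know the aim and can tell their arm. The protocol's defence covers recorded gambling behaviour. It does not cover ratings of the messages.

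7. **Count.** The first model covers outcomes 1, 3, 4, 6, 7, 8, 9, 14, 16, 17 and 19, which is 11 outcomes. Two of these 11, and 2 of the 19 primary outcomes, are concerned. With one score per outcome there are 2 contrasts and 2 × 4 = 8 moderator tests. If each scale and component is analysed separately (an assumption, as the article does not say), there are 2 + 4 = 6 contrasts and 6 × 4 = 24 moderator tests.

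8. **Outcomes 36-42.** Recall (38-42) and credibility (36-37) follow debriefing in the stated order. Outcome 36 measures "level of certitude when they were betting their own money and that they could lose money for real during the study", and the low end of its scale is near-certainty of getting the money back. Ethical Considerations says participants learn at debriefing that losses are returned. Hindsight would plausibly push answers towards that end, but the size cannot be derived from the document.

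**The case against.** The strongest reply concerns outcome 19. The between-group label shows that a comparison was intended, three of its four components name no object, controls do meet a pop-up on the machine, and both arms see the recall list. The questionnaire itself is not shown. This stands in part. A reader might infer that all four components of outcome 19 lack any valid control value, and the article does not establish that. It shows that the control stimulus is not stated, and that the most likely one gives a narrower contrast than the title promises. The reply does not help outcome 16.

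A second reply is that the post-debriefing timing of 16 and 19 is not stated. That is correct, and it is treated here as a close inference. The objection to the contrast on 16 does not depend on it.

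A third reply is that outcomes 36-42 are only described, and that asking about refunds or prevention messages before debriefing would itself expose the deception. Both points hold. A reader might infer that a test is invalidated there or that the questionnaire order is an error; the documents support neither. What remains is a caveat on interpretation, which matters most for research question 5.4, because the Discussion says the results will show whether the deception worked.

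Finally, the gambling behaviours observed in the session are recorded before debriefing, and the Discussion names a reduction in money bet as the optimal benefit. Nothing here weakens those outcomes.

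**Conclusion.** The point holds and should be fixed. For outcome 16 the planned between-arm ANCOVA and its moderator tests have no interpretation as a message effect, whatever the p-value. For outcome 19 the same is true unless a control stimulus is defined, and then the claim must be limited to that contrast. Both are very probably collected unmasked, and the protocol's defence does not reach them.

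The extent is 2 of 19 primary outcomes. No bias can be quantified, and no sample size or power figure changes. The conclusion on 16 rests on the stated definition, exposure and model. The conclusion on 19 assumes that the article omits no control stimulus defined elsewhere. The timing rests on matching both outcomes by subject to the questionnaire on cognitive and emotional response. It would be too strong to read this as a flaw in the trial's main behavioural comparison.

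**What to change.** - Remove outcome 16 from the first model, including its moderator tests. Report it descriptively with 95% CIs in experimental participants who were shown at least one message. The first message comes 10 minutes into the session, so anyone who stops earlier was not exposed. This is a description of an exposed subgroup and not a randomised comparison.
- Do the same for outcome 19, or state exactly what controls rated and limit the interpretation to that contrast.
- Record this as a dated, reasoned change made after recruitment ended in December 2024, since it alters the analysis of primary outcomes.
- Label outcomes 16, 19 and 36-42 as collected after debriefing where that is so, and do not present outcome 36 as an unbiased answer to question 5.4.

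Two further steps may suggest themselves, but I would not take them. Outcomes 32-33 cannot replace the deception check: they ask how using one's own money affected realism, not whether the participant believed it was at risk, and in alternative scenarios 2 and 3 they also follow debriefing. Nor do I ask for debriefing to be moved: final consent is confirmed there, and the later questions would themselves give the deception away.

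The cost is wording, a smaller first model and the loss of one or two between-arm tests that have no valid interpretation as planned. No new data are needed.

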#### Secondary Outcome

Table 4 shows the secondary outcome measures.

**Table 4. T4:** Secondary outcome measures.

Outcome category	Outcome number	Outcome	Description	Measurement time points
Feasibility: Recruitment potential
	20	Volunteers	Number of people that answered the recruitment ad and wanted to either participate or get more information on the study.	N/A^a^
	21	Recruited	Number of people that qualified and agreed to participate in the study.	N/A
	22	Rejected	Number of people that volunteered to participate but did not qualify according to the inclusion and exclusion criteria.	N/A
	23	Refusal	Number of people that qualified for participation in the study but refused to do so after hearing the details of it.	N/A
	24	Refusal reasons	N/A	N/A
	25	Attrition	Number of people that qualified and agreed to participate in the study but desisted during their participation.	N/A
	26	Attrition vs previous study	Conversion from recruitment list from a previous study	N/A
Feasibility: Perceived realism
	27	Gambling location type most resembling the session in the laboratory	Among a predetermined list of gambling location type (eg, bar, restaurant, casino, etc), the participant chose which of the gambling sessions in the laboratory resembled the most.	Assessed at the end of the gambling session
	28	Session in the laboratory versus gambling on EGMs in a bar/restaurant	Level of resemblance between a gambling session on EGMs^b^ in a bar or restaurant and the gambling session in the laboratory. Evaluated with a 7-point Likert scale (1=“Almost 100% different” to 7=“Almost 100% the same”).	Assessed at the end of the gambling session
	29	Similarities between sessions in the laboratory versus gambling on EGMs in a bar/restaurant	Things that were the same or very alike when comparing a gambling session on EGMs in a bar or restaurant and the gambling session in the laboratory. Participant lists all the resemblances that come to their mind.	Assessed at the end of the gambling session
	30	Differences between session in the laboratory versus gambling on EGMs in a bar/restaurant	Things that were not the same or not very alike when comparing a gambling session on EGMs in a bar or restaurant and the gambling session in the laboratory. Participant lists all the differences that come to their mind.	Assessed at the end of the gambling session
	31	What could be done to heighten the realism of the session in the laboratory	Things or aspects of the study that could be changed in order for the gambling session in the laboratory to be more like a real gambling session on EGMs in a bar or restaurant. The participant lists all that come to their mind.	Assessed at the end of the gambling session
	32	Effect of using one's own money on realism	Effect of gambling one’s own money in this study on the level of realism. Evaluated with a 7-point Likert scale (1=“It lessened the realism a lot” to 7="It heightened the realism a lot").	Assessed at the end of the gambling session
	33	Effect of using one's own money on realism (open-ended)	Effect of gambling one’s own money in this study on the level of realism. Participants freely explain their perception of the said effect.	Assessed at the end of the gambling session
	34	Perceived correspondence between habitual gambling behavior and gambling behavior during the session in the laboratory	Participant’s perception of how much their gambling behavior during their gambling session in the laboratory was representative (ie, how much it was the same) of their gambling behavior on EGMs in the past 12 months. Evaluated with a 7-point Likert scale (1=“Almost 100% different” to 7=“Almost 100% the same”).	Assessed at the end of the gambling session
	35	Perceived correspondence between habitual gambling behavior and gambling behavior during the session in the laboratory (open-ended)	Participants’ perception of how much their gambling behavior during their gambling session in the laboratory was representative (ie, how much it was the same) of their gambling behavior on EGMs in the past 12 months. Participants freely explain their perception.	Assessed at the end of the gambling session
Feasibility: Duplicity check
	36	Protocol credibility	Participant’s level of certitude when they were betting their own money and that they could lose money for real during the study. Evaluated with a 7-point Likert scale (1=“Almost 100% certain they were going to get their money back at the end of the study” to 7=“Almost 100% certain winnings and losses were real”).	Assessed at the end of the gambling session
	37	Protocol credibility (open-ended)	Participants comment freely on their level of certitude that they were betting their own money and that they could lose money for real during the study.	Assessed at the end of the gambling session

a N/A: not available.

b EGM: electronic gambling machine.

